### Procedure

#### Inclusion and Exclusion Criteria

We will only allow primary caregivers (foster or adoptive) of youth in care aged 8 to 13 years. Families indicating acute child endangerment during the web-based screening assessment (using 5 self-developed items) will be excluded. We will further exclude caregivers with an insufficient knowledge of German language, short-term foster families (“Bereitschaftspflege”), or kinship care (“Verwandtenpflege”). Excluded families will be provided with professional advice and referrals for services if desired.

#### Recruitment

We will recruit via a national association for foster and adoptive parents (Bundesverband der Pflege- und Adoptivfamilien), regional youth welfare institutions, and self-help organizations in Germany. Furthermore, we have active social media campaigns running to support recruitment.

#### Randomization and Blinding

Families will be randomized to 1 of the 16 experimental conditions via a database that uses concealed, computer-generated [63], permuted block randomization, with stratification by child’s gender and with fixed block sizes of 16 (conditions were randomized within each block). Randomization procedures will be completed by another research group within the EMPOWERYOU consortium that is not associated with the intervention trial otherwise (Neuropsychology at the University Hospital Aachen, Germany) to minimize the occurrence of potential biases (eg, biases that may arise through primary caregivers’ or researchers’ preferences). Study staff at the University of Bremen will not view the allocation sequence to minimize researchers’ prediction biases. The database will not reveal participants’ treatment conditions to the study staff until after the family’s eligibility is verified (after preintervention assessment). Families will be informed of their allocation status after baseline data collection is completed to ensure that participants are blind to allocation during the initial assessment. In the case of instances of harm or severe abuse to a child being reported by a participant, the allocation status of the participant will be unblinded. All cases of unblinding will be reported to the Data Safety and Monitoring Board (DSMB).

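### Fixed blocks of 16 with one slot per condition leave some allocations predictable if the staff who verify eligibility can see earlier families' conditions

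*Protocol article*

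**What the plan says.** All of the relevant text is in the protocol article, section Randomization and Blinding.

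- Allocation: "Families will be randomized to 1 of the 16 experimental conditions via a database that uses concealed, computer-generated" permuted blocks.
- Stratification and block size: "with stratification by child’s gender" and "with fixed block sizes of 16 (conditions were randomized within each block". The block size equals the number of conditions, so each condition fills one slot per block in each stratum.
- Separation: "Randomization procedures will be completed by another research group within the EMPOWERYOU consortium" that has no other part in the trial.
- Safeguard and its purpose: the Bremen study staff "will not view the allocation sequence to minimize researchers’ prediction biases".
- Timing of release: the database does not reveal "treatment conditions to the study staff until after the family’s eligibility is verified (after preintervention assessment".

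The section does not say which staff verify eligibility, which staff then see a family's condition, or whether the two groups overlap. It describes neither a varying nor an undisclosed block size. The Results section describes recruitment as still open, with 181 families recruited by October 2022.

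**The concern.** The safeguard hides the list. It does not hide the history of assignments from anyone who sees conditions as they are released. With a fixed block and one slot per condition, that history shows what is left in the block, and the only stratifying variable is child's gender, a basic family characteristic. Someone who knew the earlier conditions in a stratum could therefore form an expectation about the next family before deciding on its eligibility.

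At stake is selection at entry. Admission, deferral or encouragement of a family could come to depend on the expected condition. My Coach is the component most likely to matter, because it uses staff time: Textbox 3 describes 50 minutes of telephone assistance per call. The plan's declared aim is to minimise prediction by researchers, so it is fair to ask whether the chosen block structure serves that aim.

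**Working it through.** **Inputs.** From Randomization and Blinding: 16 conditions, fixed block of 16, stratification by child's gender. From Table 1: each component is on in 8 conditions and off in 8. From Sample Size Calculations: N = 317. From Results: 181 recruited by October 2022. Assumptions: two gender strata (the number is not stated), and an observer who tracks every earlier condition by gender and knows where blocks begin.

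**The plan's own figures.** The article gives no figure for predictability. Its sample size reproduces: d = 0.28, 80% power and two-sided α = 0.10 give 316 by the normal approximation and 317 by the noncentral t. For recruitment, 317/(1 − 0.26) = 428.4, so 429. Only N = 317 is used below.

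**Exact condition.** With k slots left, the best guess is right with probability 1/k. Averaged over the block this is (1/16) × (1 + 1/2 + … + 1/16) = 3.381/16 = 21.1%, against 1/16 = 6.25% by chance. The 16th slot is certain, the 15th is 1 in 2, the 14th is 1 in 3 and the 13th is 1 in 4.

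**One on/off component (8 on, 8 off per block).** Guessing the level used less often so far is right in a proportion [8 + (2^16/C(16,8) − 1)/2]/16. With 2^16/C(16,8) = 65,536/12,870 = 5.092, this is (8 + 2.046)/16 = 62.8%, against 50%.

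The level is forced when all k remaining slots share it, which has probability 2·C(8,k)/C(16,k):

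| Slot | Slots left (k) | This component forced | At least one of four components forced (simulated, 40,000 blocks) |
|---|---|---|---|
| 12 | 5 | 2.6% | about 10% |
| 13 | 4 | 7.7% | about 30% |
| 14 | 3 | 20.0% | about 63% |
| 15 | 2 | 46.7% | about 93% |
| 16 | 1 | 100% | 100% |

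Summed over all slots, the expected number of forced allocations for one component is 16/9 = 1.78 per block, and 1.78/16 = 11.1%. No component can be forced in the first eight slots.

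**Number of certain allocations.** 317/16 = 19.8. Split over two strata this gives 18 or 19 complete blocks, hence 18 or 19 fully determined allocations over the whole trial. If the 181 recruited families were all randomised, 317 − 181 = 136 remained, and 136/16 = 8.5, so roughly 8 last-slot allocations were still to come.

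**Effect of a larger block.** A block of 32 with its size known lowers the best-guess rate for the exact condition from 21.1% to about 18.0%, and the share of fully determined allocations from 6.25% to about 3.2%. Leaving the size undisclosed and mixed would lower both further, by an amount not computed here.

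**The case against.** The strongest reply concerns the premise. A reader might infer that the plan shows every condition, one by one, to the people who verify eligibility. The text does not say so. It sets the earliest time of release and names study staff in general. The same section provides for unblinding a participant's allocation after a report of harm or severe abuse, with every such case reported to the DSMB. That provision would have little purpose if all staff already knew all allocations. Coaches must know the coach component for the families they call, but nothing says that coaches verify eligibility. An article may well leave this division of roles to the full protocol. This part of the objection stands, so the point has to be conditional.

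Second, there is little room to act on a guess. Under Inclusion and Exclusion Criteria, child's age, foster or adoptive status, short-term care and kinship care are matters of fact, and endangerment is screened on the web by five items. Only sufficiency of German looks open to judgement. Registration and consent are online. The planned 26% dropout before allocation (429 − 317 = 112 families) also makes it harder to foresee who takes the next slot, although it is equally a period in which uneven encouragement would go unseen. This largely stands.

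Third, the percentages are ceilings. They need complete tracking, in order, by gender, with known block boundaries. This stands too.

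None of this removes the structural point. Within these blocks, keeping the list from staff does not keep its remaining content from someone who knows the history, and the text does not exclude that the verifiers are such people.

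**Conclusion.** The point holds as a modest, conditional weakness. If eligibility verifiers can see earlier families' conditions, the fixed one-slot-per-condition block leaves part of the sequence predictable: the last slot with certainty, a single component's level at most 62.8% of the time, and about 11% of allocations forced for that component. These figures assume perfect tracking; the counts of complete blocks also assume two gender strata. Predictability is concentrated in the last few slots of a block.

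A reader might go further and conclude that concealment has failed, or that the component effects are biased by selection. The documents do not support that. They report no misuse, they do not place verifiers and conditions in the same hands, and the largely factual web screening limits what a guess could achieve. No bias in any component effect has been quantified. The case for change is that it is cheap and serves an aim the plan states for itself.

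**What to change.** For families not yet randomised:

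1. Complete the blocks in progress under the existing list. The independent group then generates the rest with randomly mixed blocks of 16 and 32 within each gender stratum, without disclosing the sizes to study staff.
2. Set database permissions so that whoever verifies eligibility cannot see earlier families' conditions. This also covers the open blocks (at most two, one per stratum, if there are two strata), which the new list does not reach. If the roles are already separated in this way, one sentence in Randomization and Blinding saying so is enough for this step.

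The cost is a new list from a group already in place, a permission change, and submission of the change to the institutional review board, as the Ethics Approval section requires for any protocol change. Imbalance at the end may grow slightly. Within a stratum, an incomplete block of 16 leaves conditions at most 1 family apart and an incomplete block of 32 at most 2, so over two strata the largest gap rises from 2 to 4 families, against about 20 per condition (317/16 = 19.8). The benefit shrinks as recruitment proceeds: on the October 2022 count it concerns about 136 families and roughly 8 last-slot allocations.

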### Informed Consent

Informed consent will be obtained from each participant (caregiver and child) on the web. Interested study participants can register on the website and then receive the information sheet and consent form on the web. The caregivers are informed about the objectives, study procedure, the rights and obligations of all those involved, and the procedure and data processing using the information and consent forms. If the participants have any questions about the documents or the study, they can call the study team at any time. The phone number will be clearly indicated on the website. Each caregiver is asked to provide active opt-in consent for their own participation and the participation of their child in care. Multimedia Appendix 4 provides the informed consent form in German language.

### Intervention

#### Intervention Accessibility and Orientation

Caregivers will use a password to access the program (Figure 2). All parents will be offered to participate in a “welcome call” with the coach before starting with the first module. During the phone call, the procedure of the intervention and the adverse event assessment will be explained.

**Figure 2 figure2:**
[figure not shown]
Website of the EMPOWERYOU program for caregivers.

#### Duration to Complete Each Module

During the program, parents will have 2 weeks to complete 1 module, with each module taking about 90 minutes to work through (including “homework” in the form of exercises with the child).

#### Duration of the Intervention Package

Caregivers can work through the web-based program for a maximum of 10 weeks (conditions with the 3 candidate components *on* resulting in 6 weeks plus 4 weeks for the 2 basic modules). The duration of the intervention is reduced by up to 4 weeks if caregivers receive the basic modules only (experimental condition 1; Table 1).

#### Content of Each Module

We have 6 intervention modules out of which only 4 will be put to test because modules 1 and 2 are already well investigated, with promising mental health benefits for the participants besides revictimization outcomes [20,21,64,65]. In addition to the 2 “basic modules,” a website area with literature recommendations and information texts on child maltreatment, self-injury, and suicidal behavior allows us to offer some level of support across all conditions, including the condition with the lowest component level across all intervention modules. The 6 intervention modules are described in detail in Textbox 3.

The 6 modules are embedded in a common website and independent of family assessment. The assessment is conducted via a professional tool for web-based surveys (refer to the *Data Collection for the Primary and Secondary Outcomes* section). The web-based intervention includes various multimedia features (texts, slides, videos, fictional audio recordings, and interactive tasks) to make the program easily accessible and attractive.

The intervention modules.
**Module *My power, your power*—facilitating parental self-care and the self-worth of the child**
Caregivers learn how to recognize their own needs and how to implement resources-enhancing strategies in everyday life. Caregivers are encouraged and guided on how to facilitate their partnership quality (as an important resource for the caregiver and the child) and how to promote the child’s self-worth.
**Module *Our feelings*—facilitating the emotional regulation of the child and the caregiver**
The second module provides basic knowledge about emotions and their functions. Caregivers are supported in recognizing and communicating their emotions as well as the child’s emotions. Parents are encouraged to attend to their child’s emotional needs, reflect on their emotions, and learn to keep them separate from their own emotional state, or at least recognize the difference and attempt to understand their child’s emotional reactions (eg, through storytelling and behavior attribution exercises). Emotional regulation strategies for the parent and the child are introduced and practiced.
**Module *Watch Out!*—improving relationship-related risk detection and the self-protective behavior of the child**
Parents gain access to information on how they can support their child in noticing and processing risk signals (eg, combining risk signals). Exercises with the child that provide access to knowledge about children’s rights, inhibit risk-taking behavior, and enhance self-protective behavior are included. Examples on how to talk (with the child) about victimization (eg, bullying experiences) are provided, and a brief section on media literacy completes this module.
**Module *You are safe here*—improving relationship-related safety and facilitating solid relationships with family and peers**
This module includes knowledge about attachment and emotional security, and parents are supported in enhancing the child’s feeling of safety in close relationships. Parents are encouraged to reflect on their own biography and that of their children to recognize functional or dysfunctional cognitions and assumptions about close relationships that may shape the way relationships are perceived or behaved in today.
**Module *Who am I and where do I belong?*—supporting the child in constructing an identity**
The aim of this module is to support caregivers in helping their child develop an identity of their choice while providing the freedom to consider potential contributing influences of the family of origin, foster family, and peers. Caregivers are supported in facilitating a multidimensional, nonjudgmental picture of the biological parents that may allow the child to identify with their strengths. Parents are provided with practical assistance on how to reconcile the child’s needs for social belonging and autonomy and how to prevent or reduce potential loyalty conflicts and associated distress across family members.
**Module *My Coach*—providing professional support to the caregiver**
Professional support is provided to the caregiver in the form of 1 phone call per experimental module and 1 joint call for the basic modules with a coach. Coaching sessions include feedback on the caregivers’ progress in enhancing the elaboration of module content and discussing related issues in the family. The coach answers questions about program content, homework, and the transfer of knowledge and activities in their everyday family life. The participants in conditions with coach assistance *on* receive 50 minutes of additional assistance via phone (per call) as well as either an SMS text message or an email with the core message of the module.

### Data Collection for the Primary and Secondary Outcomes

Each participant will be assessed on the web using *SoSci Survey* [66] 3 times, that is, at preintervention assessment (week 1), postintervention assessment (week 12), and 3-month follow-up assessment (week 24). Families will complete a brief questionnaire (5 minutes) on adverse events and child behavior during the past 2 weeks at the beginning of each module on the program website to ensure a closely monitored adverse event assessment. Multimedia Appendix 5 outlines the SPIRIT-recommended schedule of enrollment, interventions, and assessments. Families will receive a reimbursement of €30 (US $29.32 in the form of 2 vouchers: €20 (US $19.55) for caregivers and €10 (US $9.77) for the child) for their study participation after follow-up assessments.

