### Study Design

The EMPOWERYOU project (funded by the German Ministry of Education and Research, Project code FKZ 01KR1806D) aims to develop and optimize a web-based parenting program by using the MOST framework [22]. This study will use a 2×2×2×2 full factorial design by randomly allocating participants to 1 of 16 experimental conditions (Table 1). To estimate the main effects of the 4 intervention components and their interactions, data from all the experimental conditions will be used. For example, the effect of the component *Relationship-related risk* will be estimated by comparing the mean of the experimental conditions 1 to 8 with the mean of the conditions 9 to 16 (Table 1). Families in the first condition will not receive any experimental component but will be delivered the 2 basic intervention modules that every caregiver receives. Families will be informed that everyone may access all modules and that the sequence and timing of each module will be based on a randomization procedure.

**Table 1 table1:** Experimental intervention conditions (optimization schema).

Experimental condition	Component 1: *Watch Out*!—relationship-related risk	Component 2: *You are safe here*—relationship-related safety	Component 3: *Who am I and where do I belong?*—identity	Component 4: *My Coach*—professional support
1	Off^a^	Off	Off	Off
2	Off	Off	Off	On^b^
3	Off	Off	On	Off
4	Off	Off	On	On
5	Off	On	Off	Off
6	Off	On	Off	On
7	Off	On	On	Off
8	Off	On	On	On
9	On	Off	Off	Off
10	On	Off	Off	On
11	On	Off	On	Off
12	On	Off	On	On
13	On	On	Off	Off
14	On	On	Off	On
15	On	On	On	Off
16	On	On	On	On

^a^Not included in the intervention.

^b^Included in the intervention.

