### Data Monitoring

An independent DSMB will provide additional oversight on data safety, ethical procedures, and best clinical practices. A thorough data safety concept was developed and piloted in phase 1. This safety protocol outlines how adverse events will be identified, registered, acknowledged, and handled.

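### The adverse-event questionnaire described is triggered by module starts, so how often and how long a family is asked depends on its randomized content

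*Protocol article*

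**What the plan says.** The article describes one adverse-event instrument, in the section Data Collection for the Primary and Secondary Outcomes. It is a brief "questionnaire (5 minutes) on adverse events and child behavior during the past 2 weeks at the beginning of each module", and its stated purpose is "to ensure a closely monitored adverse event assessment".

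The number of modules comes from Study Design and Table 1. A family in condition 1 gets no experimental component but "will be delivered the 2 basic intervention modules that every caregiver receives". Components 1 to 3 each add one web module when on. My Coach adds phone calls and a message, but no web module.

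On timing, "parents will have 2 weeks to complete 1 module" (Duration to Complete Each Module), and "Caregivers can work through the web-based program for a maximum of 10 weeks" (Duration of the Intervention Package).

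All families are also assessed at weeks 1, 12 and 24. The article describes outcome, mediator and moderator measures there, including victimization and bullying over the last 3 months, and does not name adverse events. Under Data Monitoring it points to a further document: "This safety protocol outlines how adverse events will be identified, registered, acknowledged, and handled". The schedule of assessments is in Multimedia Appendix 5. Neither document is shown.

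**The concern.** The trigger for asking about harm is an event that randomization controls. A family with more content modules passes more module starts, is asked more often, and is asked over a longer stretch of the programme. With identical true risk, more events would be recorded where more content is on.

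The trigger also leaves the end of the programme open. The last questionnaire comes at the start of the last module and looks back 2 weeks, so that module and the weeks after it are outside the instrument. A family that stalls never reaches the next questionnaire, and it is one whose experience a safety monitor would want to know.

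At stake are the completeness of safety monitoring and the comparability of any harms table by component. The article says that reported harm or severe abuse leads to unblinding and a report to the data safety board, so more frequent prompting could also produce more such reports in conditions with more content.

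**Working it through.** **Inputs**
- One questionnaire per module start, 2-week recall (Data Collection).
- Two basic modules for every family (Study Design).
- k = number of components 1 to 3 that are on, from 0 to 3 (Table 1).
- Two weeks per module; My Coach adds no programme weeks (the two Duration sections).
- Common assessments at weeks 12 and 24 (Data Collection).

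**Step 1: the plan's own figure.** Modules m = 2 + k; programme weeks = 2 × m. With k = 3, m = 5 and the length is 10 weeks, as stated. With k = 0, m = 2 and the length is 4 weeks, which is 10 − 4 = 6 weeks shorter. The same section says "The duration of the intervention is reduced by up to 4 weeks if caregivers receive the basic modules only". The two statements must be reconciled. The questionnaire count does not depend on it, because condition 1 has two module starts either way.

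**Step 2: count per condition.** Questionnaires = m. The first looks back to before the programme, so windows after programme start = m − 1. The last questionnaire falls at programme week 2 × (m − 1). Weeks are counted from programme start, at the 2-week pace.

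| Content modules on | Conditions | Questionnaires | Windows after start (weeks covered) | Last one at week | Weeks left to week 12 | Weeks left to week 24 |
|---|---|---|---|---|---|---|
| 0 | 1–2 | 2 | 1 (2) | 2 | 10 | 22 |
| 1 | 3–6, 9–10 | 3 | 2 (4) | 4 | 8 | 20 |
| 2 | 7–8, 11–14 | 4 | 3 (6) | 6 | 6 | 18 |
| 3 | 15–16 | 5 | 4 (8) | 8 | 4 | 16 |

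**Step 3: on against off.** For any one content component, the other two are each on in half of the conditions and add 1 module on average.
- On: 2 + 1 + 1 = 4.0 questionnaires. Off: 2 + 0 + 1 = 3.0. Ratio 4.0 / 3.0 = 1.33.
- Windows after programme start: 3.0 against 2.0. Ratio 1.5.
- My Coach: 2 + 1.5 = 3.5 at both levels. Ratio 1.0.

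If the event rate per 2-week window is the same everywhere, the expected raw count is that rate times the number of windows, so these ratios carry over to recorded counts.

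**Step 4: illustration.** The article gives no adverse-event rate, so a range is assumed. With risk p per 2-week window, the chance that at least one event falls in a window after programme start is 1 − (1 − p)^(m − 1).

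| Assumed p | 2 modules | 5 modules |
|---|---|---|
| 2% | 2% | 8% |
| 5% | 5% | 19% |
| 10% | 10% | 34% |

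The columns differ although the true risk is the same.

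**The case against.** The strongest reply is that this is a condensed article. It does not say that the questionnaire is the sole source of adverse-event data. It leaves identification of adverse events to a safety protocol and the schedule to Multimedia Appendix 5. A reader might infer that adverse events are asked about at module starts and at no other time, or that nobody is asked after starting the last module. The documents do not support that, because the inference rests on silence while two relevant documents are not shown. This part of the reply stands.

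Second, victimization and bullying are asked of all families, by parent and child report with 3-month recall, at weeks 12 and 24. That important class of harm is therefore covered after the last module on a schedule that does not depend on module progress. It would be wrong to say that harms in the last module, or in families who stop, go unrecorded altogether. This also stands, but only for victimization: adverse events in general are not described at those visits.

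Third, the plan names no comparison of harms between on and off. The selection steps use the primary outcome, interactions, mediation and cost. A reader might infer that the imbalance biases a decision of this trial; nothing in the article says so.

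Fourth, the imbalance concerns the three content components and not My Coach, and the larger ratio of 1.5 applies only when the pre-programme window is left out. Using completed questionnaires as the denominator would remove the inflation of counts. It would not restore the last module, the weeks after it, or the windows of stalled families.

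None of this changes the stated rule: the one instrument described has a frequency and span set by assignment.

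**Conclusion.** The point holds for the questionnaire that the article describes. It is given 2 to 5 times according to randomized content, and at the stated pace its windows after programme start span 2 to 8 weeks. Raw counts would be about 33% higher with a content component on at equal true rates, and about 50% higher for windows after programme start. Both figures assume that every family starts every assigned module, that modules run at the 2-week pace, and that the event rate per window is constant. At that pace the instrument leaves the 4 to 10 weeks before week 12 uncovered, and does not follow families who stall.

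It is not established that the trial as a whole lacks later adverse-event questions; that depends on the safety protocol and Multimedia Appendix 5. The point concerns safety monitoring and the reporting of harms. It does not touch the primary analysis or the choice of components.

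**What to change.** - Send the same 5-minute web questionnaire by calendar, every 2 weeks from baseline to week 12, to all families in all 16 conditions. Include those who are behind or have stopped using the programme.
- Repeat the adverse-event items at weeks 12 and 24, and state the recall period at week 24, since 2 weeks would reach back only to week 22.
- If the safety protocol or Multimedia Appendix 5 already provides this, say so in the article's Data Collection or Data Monitoring section; no change of schedule is then needed.
- For families already enrolled on the module-triggered schedule, report events per completed questionnaire window and do not compare raw counts across content levels.
- Reconcile the two statements on programme length for families with the basic modules only.

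**Cost.** A questionnaire at baseline and at weeks 2, 4, 6, 8, 10 and 12 makes 7. That adds 7 − 5 = 2 in conditions 15–16 and up to 7 − 2 = 5 in conditions 1–2, or 10 to 25 minutes per family, plus the items at week 24. The questionnaires are on the web and can be sent automatically. The real downside is two schedules within one trial: 181 families had been recruited by October 2022, which is 181 / 317 = 57% of the analysis target, so the safety data would have to be reported by schedule.
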